## Abstract

**Background:**

Small benign intestinal stenosis is usually treated by endoscopic balloon dilation (EBD) or surgery. Although EBD and surgery are able to resolve the stenosis in most cases, they are associated with several problems such as insufficient dilation and surgical stress, respectively. On the contrary, a novel approach called radial incision and cutting (RIC) is reported to have several benefits when compared to EBD and surgery. We can currently adopt RIC only for the strictures in the colon or terminal ileum and not for those stenotic lesions present further in the small intestine where balloon-assisted endoscopy is utilized, because the long-type electric knife is currently not approved for use in Japan. We will herein conduct a pilot study to investigate the safety and feasibility of RIC for treating the benign stenoses of the small intestine using the long-type electric knife.

**Methods:**

This will be a single-center, single-arm, interventional trial. The major criteria for inclusion will be age ranging from 20 to 80 years and the presence of benign stenosis in the small intestine. We will perform RIC on 10 participants. The primary outcome is the safety of this procedure, which will be assessed by measuring the frequency of adverse events of special interest. The secondary outcomes will be technical success rate, improvement in subjective symptoms, procedure time, and duration of hospitalization.

**Discussion:**

This pilot study will provide useful information that will aid in adopting RIC for treating the benign strictures present in the small intestine.

**Trial registration:**

jRCT Identifier, jRCTs022200040. Registered on 1 March 2021.

**Supplementary Information:**

The online version contains supplementary material available at 10.1186/s40814-022-01046-8.

## Background

Benign stenosis of the lower gastrointestinal tract is a common complication that physicians often encounter in clinical practice. These stenotic lesions develop due to various causes such as stricture formation at the anastomotic site after lower gastrointestinal tract surgery due to colorectal cancer [1], inflammatory bowel disease (IBD) [2, 3], and diverticulitis [4]. Other diseases and conditions, including mucosal healing in IBD, ischemic colitis [5], enteritis caused by drugs [6], and endoscopic mucosal resection of a large colorectal tumor [7], can also cause such stenotic lesions. The standard therapies for benign stenosis of the lower gastrointestinal tract are endoscopic balloon dilation (EBD) [8–11] and surgery, including resection of the stenosis [12] or strictureplasty [13]. Although surgery can definitely resolve the stenosis compared to another therapy, it is accompanied by a significant surgical stress. Some patients, especially those suffering from Crohn’s disease, develop re-stenosis and require multiple surgeries, which leads to short bowel syndrome [12, 13]. Thus, surgery should be avoided, if possible. On the contrary, EBD shows good results with a higher technical success rate and improvement in symptoms [8–11]. However, about half of the patients who undergo EBD develop re-stenosis after 3 years [9]. EBD also needs to be performed several times to obtain a certain dilation diameter, which prolongs the duration of the hospital stay. Furthermore, the degree of dilation achieved after EBD is relatively small. A prospective study reported that the rate of scope passage after EBD was only 76.3%, despite the technical success rate of 93.7% [10]. Therefore, other novel approaches for treating the benign stenosis of the lower gastrointestinal tract are required.

We previously reported the efficacy of the radial incision and cutting (RIC) method for intestinal strictures in five patients with Crohn’s disease (CD) as a pilot study [14]. RIC was initially reported as a dilation technique for refractory stenoses that developed after surgical resection of esophagogastric diseases. In this technique, the stricture is incised with an endoscopic electrical knife [15]. We adopted this method for benign stenoses of the lower gastrointestinal tract, namely those developing at the anastomotic site after ileocecal resection and rectal stenosis due to mucosal healing. Our pilot study showed a higher technical success rate (100%) and a shorter duration of hospitalization compared to EBD.

We have been conducting a continuous RIC study, which is scheduled to recruit 20 patients with benign stenosis in the lower gastrointestinal tract (UMIN000039411). We have achieved technical success in 17 cases (unpublished data). Although, delayed bleeding occurred in several cases, we secured hemostasis endoscopically in all the cases without requiring blood transfusion. RIC was also able to achieve larger diameters after dilation compared to EBD. As previously mentioned, RIC has several merits when it is used to treat benign stenosis in the lower gastrointestinal tract. However, the regions of the gastrointestinal tract for which we can adopt RIC are restricted to the colon, rectum, and terminal ileum because of the short working length of the endoscopic electric knife approved for use in Japan. The length of the endoscopic electric knife, which we can obtain in Japan, is 1850 mm, and this length is too short to reach further into the small bowel with balloon-assisted endoscopy (BAE) (working length 2000 mm). Therefore, we cannot conduct RIC for the distant stenotic lesions of the small bowel. On the contrary, a long-type electric knife with a working length of 2300 mm (FlushKnife BTS long-type, FUJIFILM, Tokyo, Japan) is approved for use in the USA, but not in Japan. If we use BAE with the long-type electric knife, we would be able to utilize RIC for all segments of the lower gastrointestinal tract. If the indication of use of RIC is expanded to include the patients with small bowel stenosis, surgery can be avoided. We herein plan to conduct a pilot study for using RIC in the treatment of small bowel stenoses.

This study aims to investigate the safety and feasibility of utilizing RIC for benign stenoses of the small intestine using the long-type electric knife, which is not approved for use in Japan.

## Methods

### Study design

This study will be a pilot study for a prospective single-center, single-arm, interventional trial. The flowchart of the study is shown in Fig. 1.

**Fig. 1 Fig1:**
[figure not shown]
Flowchart describing the study protocol. This study will target small bowel stenosis in patients with subjective symptoms. RIC will be performed in ten participants. The primary outcome is the safety of RIC being evaluated by the frequency of adverse events

### Approvals

The trial has been approved by the institutional review board of the Tohoku Certified Review Board of Tohoku University (Ministry of Health, Labor and Welfare Certified Clinical Research Review Board, Tohoku University) and is registered at jRCT (Japan Registry of Clinical Trial; jRCTs022200040, URL: https://jrct.niph.go.jp/re/reports/detail/11533).

### Setting

This study will be conducted at a single center (Tohoku University Hospital) where the investigators are well experienced in the RIC technique. Tohoku University Hospital is a tertiary referral center which serves high-level medical treatment for mainly Miyagi prefecture covering 2,000,000 people. Our division has about 2000 patients with inflammatory bowel disease and conducting endoscopic submucosal dissection (ESD) for colorectal tumors. RIC technique resembles ESD in terms of using an electric knife. The scheme of RIC is shown in Fig. 2. To our knowledge, only two institutes conduct a trial of RIC in Japan. The eligible operator is an endoscopist who experienced ESD in more than 50 cases.

**Fig. 2 Fig2:**
[figure not shown]
A The scheme of RIC from front view. Radial incision (i). Horizontal cut (ii). Complete dilation (iii). B The scheme of RIC from side view

### Population

We will include 10 patients with small bowel stenosis. This is a pilot study to investigate the safety and feasibility of RIC for small bowel stenosis; thus, the number of patients should be as small as possible. However, a certain number of participants are necessary to evaluate the safety and feasibility. Therefore, we have set the number of patients that comprise the study population at 10.

### Inclusion criteria

All the participants should meet the inclusion criteria as follows:Patients of any sex aged between 20 and 80 yearsPatients with benign small bowel stenosisPatients with performance status between 0 and 2Patients who are able to provide written informed consent for participating in the study

### Exclusion criteria

Participants with any of the following conditions will be excluded:Length of stenosis greater than 2 cmPresence of abscess or fistula close to the stenosisPresence of edematous rather than fibrotic stenosisMalignant stenosisTaking any anti-coagulant or anti-platelet drugs that cannot be discontinued temporallyPregnancy (including those in whom pregnancy is suspected), within 28 days after childbirth, or actively lactatingHistory of psychiatric diseaseHistory of severe cardiopulmonary diseaseThose who are deemed ill-suited to the study by the lead doctor

### Trial intervention

We will perform the RIC procedure in a way that is similar to that reported in previous studies [14–20]. The endoscopic electric knife used in this trial will be a Flushknife BTS long-type (FUJIFILM Corporation, Tokyo, Japan), the use of which is not covered by insurance in Japan. Although we have not specified a particular BAE for this trial, we usually use a double-balloon endoscope (FUJIFILM Corporation, Tokyo, Japan), or a single-balloon endoscope (Olympus Medical Science, Tokyo, Japan) in Japan. The schedule of RIC is shown in Table 1.

**Table 1 Tab1:** Schedule of the pilot study out-hospital

	Out-hospital		Out in-hospital	In-hospital					Out-hospital	
	Obtain consent	Screening-1	Screening-2	Enrollment	Ric	Day 1	Day 2	Day 7	Day 28	Discontinuation
Allowance duration (day)	−90 ~ −2 days	−90 ~ −2 days	−35 ~ −2 days	−2 ~ 0	±2 ~ 02	±2 ~ 02	±2 ~ 02	±2 ~ 02	±2 ~ 02	±2 ~ 02
Obtain consent	●									
Enrollment				●						
Ric					●					
Patients’ background			●							
Balloon-assisted small bowel endoscopy			●							
Computed tomography		●^d^								
Electro-cardiogram		●^d^								
Colonoscopy		▲^d^								
Abdominal ultrasound		▲^ed^								
Magnetic resonance imaging		▲^ed^								
Abdominal X-ray						●				
Body examination			●		●	●	●	●	●	●
Peripheral blood examination^a^			●			●	●		●	●
Biochemical examination^b^			●			●	●		●	●
Prgnancy test^c^			●							
Concomitant medication			●		●	●	●	●	●	●
Questionnaire: VAS			●						●	
Questionnaire: CDAI			●						●	
Adverse events					●	●	●	●	●	●

*RIC* Radial incision and cutting, *VAS* Visual analog scale, *CDAI* Crohn’s disease activity index

^a^Peripheral blood test: white blood cell, red blood cell, hemoglobin, hematocrit, platelet cell, erythrocyte sedimentation rate

^b^Biochemical test: total bilirubin, aspartate transaminase, alanine aminotransferase, alkaline phosphatase, gamma-glutamyltransferase, serum iron, total protein, albumin, total cholesterol, c-reactive protein

^c^For women with age of fertility

^d^Whether own or another facility is allowed

^e^Select either one

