### Data management and statistics

As with data collection, standard processes will be implemented to improve the accuracy of data entry and coding. A formal hypothesis testing is not appropriate because this is a pilot study to investigate the feasibility and safety of RIC for the small intestine with a small sample size. Descriptive statistics for primary and secondary outcomes described above will be conducted. We will evaluate the improvement of subjective symptoms between before and after RIC using Student’s *t* test and presenting 95% confidence intervals.

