### The study procedure and schedules

The SPIRIT checklist was followed as a guide for reporting this study protocol. It is shown in Table 1. The populated SPIRIT checklist is also provided as an additional file (see Additional file 1). We will target and screen those patients who present with subjective symptoms such as abdominal bloating, vomiting, and ileus. Most of the screening examinations will be clinical. Abdominal ultrasound or magnetic resonance imaging will be employed to investigate the wall thickness at the stenotic site as much as possible. The investigators will explain the procedure of the trial to those patients who meet the criteria and will obtain written informed consent. Participants will be able to withdraw their consent to participate whenever they want. Patients’ registration will be performed using the eligibility confirmation sheet. This pilot study is a single-arm non-randomized trial; therefore, the enrollment will be accomplished after filling out the confirmation sheet.

The enrolled participants will undergo the RIC procedure and will stay admitted to the hospital for around 7 days after RIC. Follow-up will be conducted after 1 month. The occurrence of any adverse events (AEs) will be monitored during this time. Subjective symptoms including abdominal bloating, abdominal pain, and nausea will be evaluated using VAS.

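### VAS and CDAI are scheduled only at Screening-2 (up to 35 days before RIC) and Day 28, so the before-after change can include a long pre-treatment stretch and has no score for anyone leaving early

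*Protocol article*

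**What the plan says.** All of the following is in the protocol article.

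- **Table 1 (Trial intervention).** The rows "Questionnaire: VAS" and "Questionnaire: CDAI" each carry two marks: Screening-2 and Day 28. The allowance row lets Screening-2 fall from 35 to 2 days before the reference day. Enrollment is placed from 2 days before to the day itself, so the reference day is evidently RIC.
- **Other columns of Table 1.** Physical examination and concomitant medication are recorded at Screening-2 and again on the day of RIC; the symptom scores are not. The Discontinuation column repeats every Day 28 item (physical examination, both blood panels, concomitant medication, adverse events) except VAS and CDAI.
- **Secondary outcomes; Data management and statistics.** Symptom improvement by VAS or CDAI is a secondary outcome. The analysis is given as "We will evaluate the improvement of subjective symptoms between before and after RIC using Student’s" t test, with 95% confidence intervals.
- **Study design.** "This study will be a pilot study for a prospective single-center, single-arm, interventional trial".
- **Population.** On sample size: "we have set the number of patients that comprise the study population at 10".
- **The study procedure and schedules.** "We will target and screen those patients who present with subjective symptoms such as abdominal bloating, vomiting, and ileus". Also: "Follow-up will be conducted after 1 month".

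**The concern.** In a single-arm trial, the difference between the two scores is the only evidence on symptoms. The comparison attributes everything that happens between the first and second score to RIC. If the first score is several weeks old when the procedure is done, changes in diet, medication or the course of the disease during the wait are included in the apparent effect. Patients are approached because they have symptoms, so some movement in the scores before RIC is plausible.

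The second gap is at the other end. The Discontinuation visit exists and collects other data, but no symptom score. A patient who leaves after RIC and before Day 28 has no scheduled post-RIC value, and with 10 patients each missing value counts.

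Both gaps concern what is collected. A statistical analysis plan can define a baseline or a missing-data rule, but it cannot recover a score that was never taken.

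**Working it through.** The article derives no figure on this point; the sample size of 10 is a pragmatic choice without alpha, power or effect size. The check is therefore a reading of the schedule plus interval arithmetic.

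**Inputs**
- Age of baseline at RIC: b = 2 to 35 days (Table 1, Screening-2 window).
- Time from RIC to follow-up score: f = 28 days (Table 1).
- Enrollment window: 0 to 2 days before RIC (Table 1).
- Tolerance at Day 28: the allowance cell did not survive text extraction legibly; ±2 days is assumed.

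**1. Share of the before-after interval that precedes treatment: b / (b + f)**

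| Baseline | b | b + f | Share before RIC |
|---|---|---|---|
| Screening-2, earliest | 35 | 63 | 35/63 = 55.6% |
| Screening-2, latest | 2 | 30 | 2/30 = 6.7% |
| Enrollment, earliest | 2 | 30 | 2/30 = 6.7% |
| Enrollment, on day of RIC | 0 | 28 | 0% |

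With the assumed ±2 days at follow-up, the 35-day case gives 35/61 = 57.4% to 35/65 = 53.8%. Using the Enrollment window would remove up to 35 − 2 = 33 days of pre-treatment time.

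**2. What a pre-treatment drift could do (assumed values only)**

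Take n = 10, a paired t test at two-sided 5%, no true effect of RIC, and a drift of d standard deviations of the change score before RIC. The critical value is 2.262 on 9 degrees of freedom and the noncentrality is d√10. The chance of p < 0.05 is 1 − F(2.262; 9, d√10) + F(−2.262; 9, d√10), where F is the noncentral t distribution function.

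| Assumed drift d | d√10 | P(p < 0.05) |
|---|---|---|
| 0 | 0 | 5% |
| 0.2 | 0.632 | 8.8% |
| 0.3 | 0.949 | 13.6% |
| 0.5 | 1.581 | 29.3% |

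The 95% confidence interval half-width is 2.262/√10 = 0.72 SD, so a drift of 0.2 to 0.5 SD is smaller than the half-width and could not be recognised from the data. The article gives no value for d and no sign. The calculation shows sensitivity; it does not estimate bias.

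**3. Discontinuation**

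The two score rows are blank in that column, while five other rows are marked. The article gives no discontinuation rate or reasons and does not say whether a discontinued patient still attends Day 28. The effect of the missing score therefore cannot be computed; any percentage would only restate an assumed loss.

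**The case against.** **The baseline visit is coherent.** Screening-2 also holds the balloon-assisted endoscopy, blood tests, medication and background, and 35 days is the outer limit; the visit may be only 2 days before RIC. This stands: the schedule is neither an error nor a contradiction. It still leaves the age of the baseline free to vary between patients from 2 to 35 days, when a visit closer to RIC already exists.

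**The drift may be small or adverse.** There is no entry threshold on VAS or CDAI, which weakens the argument from regression to the mean. Excluding edematous stenosis limits one source of short-term fluctuation. Symptoms may also worsen during the wait. All of this stands. A reader might infer that the old baseline flatters RIC; the article does not support that, because the direction is unknown.

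**A later baseline does not cure a single-arm design.** This is correct. Regression to the mean and placebo response remain wherever the baseline is placed. A later score shortens the untreated stretch; it does not create a control.

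**Failures are not shown to be lost.** A reader might infer that the blank Discontinuation cells selectively remove patients in whom RIC failed. The article does not say so. The only exit it states is withdrawal of consent, RIC is a single procedure, and nothing says that a failed or complicated case skips Day 28. A patient who leaves before RIC has no post-treatment score to lose. Bleeding or perforation that needs endoscopic hemostasis or surgery is in any case counted in the primary outcome.

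**The outcome is secondary.** This also stands. The article disclaims formal hypothesis testing, and its Discussion ties a larger study to safety. Even so, symptom change is the only outcome for which it names a test.

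**Conclusion.** The point holds as a limited weakness in data collection. The plan allows up to 35 of 63 days (56%) between the two symptom scores to precede RIC, against at most 2 of 30 (7%) with a score in the Enrollment window. It also schedules no post-RIC score for anyone who leaves before Day 28. These statements rest on Table 1, on reading its day counts as relative to RIC, and on a nominal 28-day follow-up.

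The documents do not show that scores drift before RIC, in which direction, or that early leavers are mainly failures. A claim that both gaps favour RIC would go beyond them. The primary outcome is untouched, and adverse events are recorded at Discontinuation. The change is worth making because it is cheap and cannot be made after the fact; the validity of the trial does not depend on it.

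**What to change.** In Table 1:

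1. Mark VAS at Enrollment, before preparation for RIC begins, and CDAI for Crohn's patients where its components are available at that visit (Table 1 schedules no blood tests there). Name this score as the baseline for the change described as "We will evaluate the improvement of subjective symptoms between before and after RIC", and keep Screening-2 as a second pre-treatment value. The two together also show how far scores move before treatment.
2. Mark VAS, and CDAI on the same condition, at Discontinuation when it occurs after RIC. Report these scores descriptively and apart from Day 28 scores, because they may be taken on any day and may reflect a recent complication.

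**Cost:** at most two short extra questionnaire sets per patient, at visits already in the schedule, with no change to treatment. The remaining limits of an uncontrolled comparison should still be stated when the results are reported.

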### Outcomes

#### Primary outcome

The primary outcome of this study is the safety of using RIC for benign stenosis in the small intestine, and the safety is evaluated by measuring the frequency of adverse events of special interest (AESI) during 1 month after RIC. AESI includes complications related to RIC, such as delayed bleeding and perforation, which require endoscopic hemostasis or surgery. Safety of RIC is selected as the primary outcome because this is a pilot study and there are no other studies reporting the safety of performing RIC in the small intestine using BAE.

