### Safety

As mentioned above, the safety of RIC is the primary outcome of this study. Bleeding and perforation after RIC are the probable major AEs. Our previous report and other studies showed that delayed bleeding and perforation were the major AEs. The participants could also develop pancreatitis after EBD via the transoral approach. These AE and other complications will be monitored until 1 month after RIC and recorded in a case report form.

Serious adverse events (SAEs) are defined as follows:All deaths and immediate life-threatening events, whether related or unrelated to the procedureProlongation of hospitalizationSubstantial disruption of normal life functions

All SAEs will be recorded as well and reported to the institutional review board and the Ministry of Health, Labor and Welfare as soon as possible.

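### The primary safety outcome ties an AESI to the treatment it needs, so a perforation managed without surgery, or a bleed treated by another route, is not clearly counted

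*Protocol article*

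**What the plan says.** The Primary outcome section of the protocol article sets the measure and window: "the safety is evaluated by measuring the frequency of adverse events of special interest (AESI) during 1 month after RIC". It then describes the events: "AESI includes complications related to RIC, such as delayed bleeding and perforation, which require endoscopic hemostasis or surgery". The Abstract and the Discussion also refer to AESI.

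Two other places describe the events differently. The Fig. 1 legend reads "The primary outcome is the safety of RIC being evaluated by the frequency of adverse events", with no restriction to AESI. The Safety section reads "Bleeding and perforation after RIC are the probable major AEs", with no reference to treatment, and adds "The participants could also develop pancreatitis after EBD via the transoral approach" without saying whether pancreatitis is an AESI. The same section provides for full capture: "These AE and other complications will be monitored until 1 month after RIC and recorded in a case report form". Table 1 schedules adverse event collection from the RIC visit through Day 28.

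The sample size is fixed by judgement (Population section: "Therefore, we have set the number of patients that comprise the study population at 10"). The Data management and statistics section plans descriptive statistics for the primary outcome and no formal hypothesis test. The Discussion makes a larger study conditional on RIC proving relatively safe, without putting a number on that.

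**The concern.** An event enters the primary count partly through the treatment it calls for, not only through what happened to the patient. Of the two treatments named, endoscopic hemostasis addresses bleeding. For a perforation, that leaves surgery as the route into the count. A perforation handled in any other way is then not clearly an AESI, although the Safety section treats perforation as a probable major event without condition. A bleed handled by a route other than the two named is in the same position.

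This matters for two reasons. First, two careful readers could classify the same patient differently, so the primary count is not reproducible from the text. Second, in an unblinded single-arm study the treating team's choice of management helps decide what is counted. The AESI frequency is the only primary outcome and the main evidence for the step to a larger study.

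**Working it through.** **1. The definitions side by side**

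| Place | Events described | Treatment qualifier |
|---|---|---|
| Primary outcome | RIC-related complications; bleeding (delayed) and perforation as examples | Yes: endoscopic hemostasis or surgery |
| Safety | Bleeding and perforation as probable major events; pancreatitis mentioned | None |
| Fig. 1 legend | Adverse events | None |

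Consider a perforation that is managed without surgery and prolongs the hospital stay. Under Safety it is a major adverse event, and a serious one, because prolonged hospitalization is on the list of serious events. Under the Fig. 1 legend it counts. Under Primary outcome it does not clearly count.

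Timing is also loose. The primary window is the month after RIC and the bleeding named is delayed, while Table 1 collects adverse events at the RIC visit itself. Whether an event during the cutting is an AESI is not stated.

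**2. Direction**

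Among bleeds and perforations, those meeting the qualifier are a subset of all procedure-related perforations plus all bleeds needing any intervention. The restricted count can therefore be equal or lower, never higher. The difference is zero if every such event needs one of the two named treatments.

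**3. Size of one reclassified event, n = 10**

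The plan states no expected AESI rate, threshold or power, so there is no figure of its own to reproduce. Exact (Clopper-Pearson) 95% intervals:

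- 0/10: lower limit 0; upper limit 1 − 0.025^(1/10) = 0.308, i.e. 0% to 30.8%.
- 1/10: lower limit 1 − 0.975^(1/10) = 0.0025; upper limit is the 97.5% quantile of Beta(2, 9) = 0.445, i.e. 0.3% to 44.5%.

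One event moves the observed rate by 10 percentage points.

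**4. Illustration for bleeding**

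The Discussion cites 8.8% delayed bleeding with RIC, from another study whose bleeding definition is not given. The share s of bleeds that would meet the qualifier is not in the documents, so it is an assumption and is varied here. Expected counted bleeds = 10 × 0.088 × s. Chance of at least one = 1 − (1 − 0.088 × s)^10.

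| Assumed s | Expected counted bleeds | Chance of at least one |
|---|---|---|
| 100% | 0.88 | 60.2% |
| 75% | 0.66 | 49.5% |
| 50% | 0.44 | 36.2% |
| 25% | 0.22 | 19.9% |

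The Background reports that every delayed bleed in the ongoing RIC study was controlled endoscopically and none needed transfusion. That points to s near 100%, so the lower rows are a range, not a forecast. The documents give no perforation rate, so the same calculation cannot be done for perforation, where the definition is weakest.

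**The case against.** The strongest reply is that the sentence is not exclusive. It introduces examples in an open list, and it speaks of events that require a treatment, not events that received it. This stands in part: the text never says that nothing else counts. But openness does not settle whether a given perforation is in or out, and whether a treatment was required will in practice be judged largely from what was done.

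A second reply is that complications needing intervention are a legitimate severity-based endpoint, and that a count of them is unbiased for that quantity. This also stands. A reader might infer that the safety result is biased low. The documents do not show that; they show only that the count can be lower than a count defined by event.

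A third reply is that nothing is lost: all adverse events are recorded for 1 month and serious ones are reported. That is correct. The defect lies in what the primary outcome counts, not in data capture.

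A reader might also infer that a single misclassified event decides the trial. With descriptive analysis, no AESI threshold and two heavily overlapping intervals, there is no decision rule for one event to flip.

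On pancreatitis, a reader might take the lack of a pancreatic enzyme in the Table 1 biochemistry panel to mean that it would be missed. A scheduled panel does not rule out testing on suspicion, and the Safety section ties pancreatitis to EBD, which is not the trial procedure. An added test is not called for.

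Finally, a condensed article may leave detailed criteria and grading to the full protocol. That would answer a complaint of missing detail. Here the article does state a rule, and the three places that describe the outcome do not agree.

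**Conclusion.** The point holds as a fault in the endpoint definition, worth a cheap correction, and not as a demonstrated bias. The AESI rule combines an open list with a treatment qualifier, and the Primary outcome section, the Safety section and the Fig. 1 legend do not describe the same set of events. A perforation managed without surgery is the clearest case whose status is unsettled. For bleeding, the sponsor's own experience suggests little practical effect.

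The direction (equal or lower) follows from the restrictive reading alone. The size is unknown, because the share of events outside the qualifier is not given. Each such event, if it is a patient's only one, changes the result by one patient in ten.

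**What to change.** Define AESI by event, from the start of the RIC procedure to Day 28:

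- any procedure-related perforation, whatever its management;
- any procedure-related bleeding that leads to an unplanned intervention of any type;
- any other procedure-related event needing surgery.

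State whether pancreatitis is included. Report the present intervention-based definition as a supportive subset, so that the severity information is kept. Reconcile the Primary outcome section, the Safety section and the Fig. 1 legend, and clarify the reference to EBD in the pancreatitis sentence. Settle this before any event is classified.

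The cost is protocol wording only, since the events are already collected from the RIC visit to Day 28. The one downside is that the reported AESI rate may be slightly less favourable.
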